## 3. Expected Study Population

Among the 2360 participants aged ≥20 years who were newly enrolled at Visit 3 of the CCHS, 374 reported cardiovascular, kidney, and liver disease, or diabetes, and an additional 117 participants reported use of related medicine, leaving 1869 healthy participants at baseline. Of these, 728 did not participate in the follow-up visit, and 304 did not participate in the outcome assessment visit, resulting in 837 individuals with full participation. 102 had one or more missing baseline covariates, and 2 had missing time-varying covariates, leaving a final study population of 733 participants. Of these, 38 participants did not provide consent for the use of their blood samples, leaving 695 participants potentially eligible for blood-based analyses. We expect that approximately 40 of the potentially eligible participants will have missing or insufficient blood samples from at least one of the two visits required for PFAS measurement and therefore will be excluded from the final study sample. A flow chart can be seen in Figure 5.

## 4. Methodological Considerations

In an attempt to move beyond conventional exposure-outcome analyses, we explicitly followed the TARGET Statement [24] to articulate a well-defined causal question and to align eligibility criteria, intervention strategies based on observed reduction in PFAS, outcome timing, follow-up, and causal contrasts with a hypothetical PFAS counseling trial. This framework allowed us to transparently document the design choices and assumptions required to emulate such a trial using long-term data from the CCHS.

The CCHS will allow us to leverage temporally separated measurements of PFAS concentrations, with the serum lipids outcome assessed at a subsequent visit, thereby ensuring temporality between exposure and outcome. The 10-year interval between PFAS measurements improves the ability to distinguish new exposure from residual baseline levels. Consequently, the change between the two PFAS measurements more strongly reflects PFAS exposure during the follow-up period and is therefore more informative for evaluating the causal relationship with lipid levels measured 10 years later. In addition, the study will benefit from rich longitudinal covariate information collected through questionnaires and clinical examinations from the CCHS, as well as from national registries, which will support the exchangeability assumption through adjustment for all identified confounders. We will also capture a period during which PFAS exposures in the general population are expected to have declined following regulatory changes, with some compounds showing steeper decreases than others [31].

Serum lipid concentrations were measured in the non-fasting state in the CCHS, consistent with current Danish and broader European laboratory practice. Non-fasting blood sampling does not affect cholesterol, which differs minimally between fasting and non-fasting states [32]. However, triglycerides are known to rise postprandially; therefore, non-fasting measurements introduce additional within-person variability related to unmeasured time since last meal [32]. Because fasting status was uniform across the cohort and unrelated to exposure status, this measurement variability is expected to be non-differential with respect to exposure and to attenuate precision rather than bias the estimated effect.

Baseline diet may be a potential confounder, as dietary habits would affect both PFAS and serum lipid levels [33], and since dietary intake was not measured at baseline in the CCHS, it may challenge the exchangeability assumption. We will adjust for baseline PFAS levels, waist–hip ratio, highest attained education, income, and cholesterol, which will also serve as proxies for baseline dietary habits. While this is true under a classical epidemiological approach with a single time-point exposure, diet poses a particular challenge beyond simple confounding when looking at PFAS change as our exposure. Behavioral dietary change (e.g., reduced consumption of animal-based foods) is part of the causal pathway through which PFAS exposure changes. Adjusting for diet change or diet as a time-varying covariate would result in conditioning on a variable that created the PFAS change itself and would therefore result in removing part of the true causal effect of PFAS exposure reduction on lipid outcomes [33]. In the emulation, we will not be able to observe and distinguish the specific pathways of PFAS reduction. This challenges the consistency assumption, because the health effect of a given PFAS reduction may differ depending on the underlying pathway. For example, reductions driven by dietary changes (e.g., lower intake of animal-based foods) could influence serum lipids through nutritional pathways independent of PFAS. In contrast, reductions due to environmental regulation would not involve these pathways. Consequently, any observed association between PFAS reduction and serum lipids may partly reflect concurrent lifestyle changes, potentially leading to an overestimation of the true effect of PFAS reduction. However, the most plausible driver of reduction in PFAS in this setting is regulatory change during the study period, which would affect exposure uniformly across the population [31]; thus, the consistency assumption likely holds.

The emulation conditions require continuous participation across all three visits as well as available serum for PFAS measurement and serum lipid data. If continuous participation is partly related to underlying health status and PFAS simultaneously influence this through their effect on health, this could lead to selection bias. Although inverse probability weighing could address this form of administrative selection, it would require costly PFAS quantification in participants with incomplete follow-up to construct censoring models. This presents a bias-variance tradeoff where the reduction in bias is outweighed by the loss of statistical precision and increased estimator variance. Given these constraints, the design choice of the emulation differs from the target trial and limits our ability to fully emulate the trial’s follow-up process. PFAS was not part of the original scope nor measured during active data collection in the CCHS, and participants were unaware of their PFAS levels at that time (PFAS will be measured from stored blood samples), minimizing the risk of self-selection due to PFAS. As illustrated by the selection-bias DAG (Figure 6), conditioning on participation may introduce selection bias, potentially inducing an association between PFAS changes and serum lipid outcomes even in the absence of a true causal effect. If participants with increases in PFAS concentrations remain in the study, they are more likely to represent a “healthier subset” with more favorable serum lipid profiles compared to the target population, potentially leading to an underestimation of the true effect of PFAS reduction. Accordingly, estimates should be interpreted as conditional on continuous study participation and may not be fully generalizable to the original target population. To assess the magnitude of this selection, we consider comparing baseline PFAS concentrations between individuals in the study population and a random sample of those who participated only at baseline, as well as at baseline and at follow-up, to get an indication of how strongly PFAS is associated with continuous participation. Based on an expected study population of 655, we would need to measure baseline PFAS for 155 individuals in each group to be able to detect a standardized mean difference in Cohen’s d = 0.25 (one-fourth of a standard deviation) using a two-sided alpha of 0.05 and 80% power. A minimum of 87 individuals would need to be measured to ensure detection of a difference no larger than Cohen’s d = 0.32 (one-third of a standard deviation). However, because PFAS testing is expensive, analyzing the samples from these additional individuals is an optional secondary analysis that will only be conducted if additional funding is secured.

We will conduct a complete-case analysis whereby participants with missing baseline or time-varying covariate data (n = 104) will be excluded. Multiple imputation was considered as an alternative approach to handling this missingness. However, imputing the missing data would require an additional costly 208 PFAS analyses (104 participants × 2 [measurements/timepoints]). To assess whether this cost could reasonably be avoided, we conducted a preliminary comparison between the 104 participants expected to be excluded due to missing covariate data and our expected study population, without accounting for additional participants who may be excluded due to missing blood samples (if any) once data collection is complete. The results of this comparison were reassuring: only small differences were observed in income, education, and smoking status between the two groups. This pattern suggests that missingness is consistent with a missing-at-random mechanism. As income, education, and smoking status are included as covariates in the analytic model, complete-case analysis is expected to yield approximately unbiased estimates under this assumption.

The CCHS draws from the general population and includes participants across all socioeconomic categories, supporting the broader relevance of our findings across social strata. The median age of our study population was 37 years, indicating a middle-aged adult population, which should be considered when comparing our results to studies conducted in younger or older cohorts. However, our strict exclusion and inclusion criteria, including exclusion of individuals with different diseases and medication at baseline, ensure that our analytic sample represents a relatively healthy population. As such, our findings may not directly generalize to individuals with pre-existing cardiometabolic disease or treatment, and should be interpreted as most applicable to healthy, middle-aged adults. Geographic location can also shape co-pollutant exposure profiles, a common source of variability in environmental exposure studies, which could potentially limit the generalizability of the results.

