#### 2.1.3. Outcome and Follow-Up Period

Outcomes of interest are serum lipid biomarkers including total cholesterol, LDL cholesterol, high-density lipoprotein (HDL) cholesterol, remnant cholesterol, and triglycerides. Follow-up would start at assignment to an intervention strategy at baseline. Loss to follow-up would include nonparticipation in the 20-year outcome biomarker assessment visit, emigration, withdrawal from the study or revocation of consent, or death. Adherence would be evaluated through telephone interview 10 years after intervention assignment. To isolate the effect of PFAS-reducing counseling from residual baseline PFAS levels, it is necessary to allow sufficient time for natural PFAS elimination to occur. For example, Perfluorohexanesulfonic acid (PFHxS) has an estimated biological half-life of approximately 5.3 years [25]. This implies that roughly 75% of baseline serum PFHxS would be naturally eliminated after two half-lives, with even greater elimination expected for the other PFAS with shorter half-lives. To obtain optimal temporal separation between adherence and the outcome, we would wait 10 years to capture long-term effects, effectively separating past exposure from current effects. The temporal structure of the target trial is presented in Figure 1.

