#### 2.2.3. Intervention Strategies and Assignment

Because no formal PFAS counseling intervention was provided in the CCHS, intervention assignment will be inferred from the observed change in serum PFAS concentrations between the baseline and follow-up visit. The change in each individual PFAS will be analyzed separately. Lower decreases in serum PFAS levels can result from routine laboratory measurement error (assay coefficient of variation, CV) rather than a true physiological change. To avoid misclassifying analytical noise as a genuine decrease, we applied a reference-change-value approach adapted from Harris and Yasaka’s framework [27]. In the primary analysis, for each participant, the laboratory-reported analytical CVs for baseline and follow-up PFAS measurements will be combined, yielding a participant-specific threshold that reflects the total measurement error expected for that individual. Increases or reductions at or below this threshold will be categorized as “increase/no true reduction”; reductions exceeding it will be categorized as “reduction”, representing a true decrease beyond measurement variability. In the secondary analysis, we will divide the “reduction” group by the median to separate lower and higher reductions. This classification aligns with an as-treated analysis, in which participants are analyzed according to their observed exposure change rather than a randomized assignment.

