#### 2.2.4. Outcome and Follow-Up Period

Outcomes will be the same as in the target trial. Total cholesterol, HDL cholesterol, and triglycerides were measured in non-fasting plasma using standard enzymatic hospital assays (Boehringer Mannheim GmbH, Mannheim, Germany; Konelab, Thermo Fisher Scientific, Waltham, MA, USA). HDL cholesterol was quantified after precipitation of apolipoprotein B-containing lipoproteins. LDL cholesterol was calculated using the Friedewald equation when triglyceride concentrations were ≤4 mmol/L (≤352 mg/dL) and was measured directly at higher triglyceride levels. Remnant cholesterol was derived as total cholesterol minus the sum of HDL cholesterol and LDL cholesterol.

Intervention strategies become observable at the follow-up visit (approximately 10 years after baseline, as data collection cycles in the CCHS were not conducted at fixed intervals and varied between participants, with a median interval of 10 years). Participants are subsequently assessed for serum lipids at the outcome assessment visit, approximately 10 years later, effectively 20 years after baseline (Figure 3). Because treatment classification is based on the change in PFAS concentrations between the baseline and follow-up visit, the emulation conditions require continuous participation across these visits; therefore, adherence is complete by design.

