#### 2.2.8. Sensitivity Analysis

First, because initiating lipid-lowering medication after baseline influences serum lipid outcomes, we will perform a sensitivity analysis in which time-varying lipid-lowering medication use is set to zero. With this, we will simulate a counterfactual scenario in which no participant initiated treatment during follow-up, allowing us to assess how post-baseline lipid-lowering medication uptake influences our effect estimates. Second, to evaluate the implications of using alternative exposure definitions applied in prior PFAS studies, we will estimate the associations between (i) baseline PFAS concentrations and serum lipid levels at the follow-up and outcome assessment visits and (ii) follow-up PFAS concentrations and lipid outcomes at the outcome assessment visit. If estimates obtained using these alternative single time-point exposure definitions differ from those derived from the target trial emulation, such discrepancies would indicate that the conventional observational approach, even when temporality is respected, may still produce biased effect estimates.

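### The 10-year interval separates new from residual PFAS exposure in the follow-up level, or in the change once baseline PFAS is conditioned on, but not in the change by itself

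*Protocol article*

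**What the plan says.** Section 2.1.3 gives the reason for waiting 10 years in the hypothetical trial: "To isolate the effect of PFAS-reducing counseling from residual baseline PFAS levels, it is necessary to allow sufficient time for natural PFAS elimination". It supports this with a figure: "Perfluorohexanesulfonic acid (PFHxS) has an estimated biological half-life of approximately 5.3 years", so that "roughly 75% of baseline serum PFHxS would be naturally eliminated after two half-lives".

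In the emulation (Section 2.2.3), "intervention assignment will be inferred from the observed change in serum PFAS concentrations between the baseline and follow-up visit". The visits are spaced "with a median interval of 10 years" (Section 2.2.4). Section 4 carries the elimination argument over to this exposure in two steps: "The 10-year interval between PFAS measurements improves the ability to distinguish new exposure from residual baseline levels", and then "Consequently, the change between the two PFAS measurements more strongly reflects PFAS exposure during the follow-up period". It goes on to call the change more informative for the causal question.

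Three other statements bear on the point:

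- Section 2.2.6 adjusts for continuous baseline PFAS only if its correlation with the change is below 0.8.
- Section 4, in the discussion of diet, states the same adjustment without a condition.
- Section 2.2.8 lists as an alternative exposure "ii) follow-up PFAS concentrations and lipid outcomes at the outcome assessment visit". It treats this as a single time-point definition, and it would read disagreement with the main analysis as a sign of bias in the conventional approach.

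**The concern.** The 75% figure describes how much of the baseline level has left the follow-up measurement. The change is follow-up minus baseline, so what has been eliminated is not removed from the change: it is a component of it. If the change carries baseline burden at any interval, people classed as reducers are to a large extent people who started high. The primary contrast then mixes past with recent exposure unless baseline PFAS is held fixed.

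Two decisions depend on this. The first is whether baseline adjustment may ever be dropped. A reader who accepts the sentence in Section 4 would think the interval already does the separating and see little harm in leaving baseline out. The second is how to interpret a disagreement between the change analysis and the follow-up-level analysis.

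**Working it through.** **The plan's own figure.** Eliminated share = 1 − 2^(−t/h). Two half-lives give 1 − 0.25 = 75%. At exactly 10 years with h = 5.3 it is 1 − 2^(−10/5.3) = 1 − 0.270 = 73%. The stated figure is sound.

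**The algebra.** Let C0 be the baseline level, S the elimination-weighted level that intake during the interval would sustain, and r = 2^(−t/h). First-order elimination gives

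- follow-up level: C1 = r·C0 + (1 − r)·S
- change: C1 − C0 = (1 − r)·(S − C0)
- relative change: (1 − r)·(S/C0 − 1)

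| Interval (h = 5.3 y) | Weight of C0 in level | Weight of S in level | Weight of C0 in change | Weight of S in change |
|---|---|---|---|---|
| 2 y | 0.77 | 0.23 | −0.23 | +0.23 |
| 5 y | 0.52 | 0.48 | −0.48 | +0.48 |
| 10 y | 0.27 | 0.73 | −0.73 | +0.73 |
| 20 y | 0.07 | 0.93 | −0.93 | +0.93 |

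In the level, the balance shifts towards new exposure. In the change, both weights grow together and their ratio stays at −1.

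**Size without baseline in the model.** The article gives no PFAS variances, so these are assumptions: C0 and S lognormal, log-SD of C0 0.6, median S/C0 0.7, no assay noise. With log-SD of S also 0.6 and C0 and S independent, the correlation of the log change with new exposure is 0.65 at 2 years, 0.69 at 10 and about 0.70 at 20. For the log follow-up level it is 0.24, 0.84 and 0.98.

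**Effect on the class contrast at 10 years.** Reduction is taken as a relative fall of more than 10% (an assumed threshold). The outcome depends only on baseline burden, one unit per log unit, so the true effect of new exposure is zero.

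| Log-SD of S; correlation with C0 | Correlation with baseline: absolute change | Same: log change | Same: relative change | Median baseline, reduction ÷ no reduction | Class contrast, baseline omitted | Baseline included |
|---|---|---|---|---|---|---|
| 0.6; 0 | −0.82 | −0.69 | −0.45 | 1.9 | 0.68 | 0.00 |
| 0.6; 0.5 | −0.74 | −0.50 | −0.38 | 1.6 | 0.49 | 0.00 |
| 0.3; 0 | −0.96 | −0.88 | −0.61 | 2.2 | 0.87 | 0.00 |
| 0.3; 0.5 | −0.96 | −0.86 | −0.65 | 2.2 | 0.85 | 0.00 |

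Including baseline removes the spurious contrast in every row. Reading the 0.8 rule as a limit on magnitude, baseline would be dropped in three of the four rows on the absolute scale, in two on the log scale and in none on the relative scale. The article does not say which scale the rule uses.

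**Change versus level, given baseline.** With C0 in the model, C1 − C0 and C1 differ by a term that is already there, so their coefficients are identical. In a separate simulation in which again only baseline burden matters (10 years, correlation of absolute change with baseline −0.86), the coefficient was −1.18 for the change alone and +1.36 for the level alone. Given baseline it was 0.00 for both. The two unadjusted analyses can therefore disagree, even in sign, without either reflecting new exposure.

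**The case against.** The strongest reply is that the primary analysis is not unadjusted. Section 2.2.6 plans a spline term for baseline PFAS, Section 2.2.7 puts those covariates in the outcome model, and Section 4 states the adjustment outright. The baseline imbalance between classes is then handled. This stands, and it limits the point. A reader might infer that the primary contrast as planned simply compares people with high and low past exposure, or that only the follow-up level can isolate new exposure, so the change should give up its primary place. The documents do not support either reading. Given baseline, the change and the level carry the same information, and reduction classes are a natural counterpart to a reduction strategy. Moving to a per-unit effect of follow-up PFAS would change the estimand.

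A second reply is that the wording in Section 4 is comparative and that a longer gap does help the change. This is partly right. A larger change stands out better from assay noise: with an assumed 10% CV, its correlation with new exposure rises from 0.52 at 2 years to 0.67 at 10. Conditional on measured baseline it rises from about 0.65 to about 0.94. The large gain thus comes from the interval together with conditioning, which is not what the sentence says.

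Third, the argument in Section 2.1.3 is not an error where it stands. The hypothetical trial randomises to counseling and uses no change score. The difficulty arises only when Section 4 applies it to the change.

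**Conclusion.** The inference in Section 4 does not hold as written. Under the article's own elimination model, the interval rescales the change but does not shift its balance between new exposure and baseline burden. What separates the two is conditioning on baseline PFAS, and the long interval makes that conditioning work better. The identity holds for any half-life and any intake pattern within the interval. It assumes first-order elimination at a common rate, and comparing intervals assumes that the distribution of S is the same at each.

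The practical consequence is moderate. With baseline PFAS in the model, the spurious contrast of 0.49 to 0.87 outcome units falls to about zero. Those sizes rest on assumed variances and show direction and order of magnitude; they do not forecast this cohort. What remains is that the 0.8 rule can remove the adjustment in the situation where the change is mostly a mirror of baseline, that Sections 2.2.6 and 4 disagree on whether the adjustment is conditional, and that Section 2.2.8 attributes any disagreement to one side only.

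**What to change.** 1. Keep the reduction classes as the primary exposure, and include baseline PFAS in every change model. Remove the 0.8 condition from Section 2.2.6 so that it agrees with the unconditional statement in Section 4.
2. In sensitivity analysis (ii), add a version of the follow-up PFAS model with baseline PFAS as a covariate. State in Section 2.2.8 that disagreement with the change analysis may come from baseline burden in either exposure, and is not evidence of bias in the single time-point approach alone.
3. Reword the sentence in Section 4 to say that the 10-year interval together with conditioning on baseline PFAS, and not the change by itself, separates new from residual exposure. The gain relative to assay noise can be mentioned as a separate benefit.

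No new assays are needed, since both PFAS measurements are already planned. The costs are some loss of precision for compounds where baseline and change are strongly correlated, and one extra model per lipid and PFAS.

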Overcoming these persistent design limitations is essential for drawing reliable inference on the effects of PFAS on serum lipids. Therefore, we aim to assess whether there is a causal relationship between PFAS and serum lipid levels by emulating a target trial of a PFAS-reduction intervention using observational data from the Copenhagen City Heart Study (CCHS). This protocol specifies the target trial and its emulation.

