#### 2.2.6. Assumptions

We will assume conditional exchangeability between intervention groups after adjustment for baseline and time-varying covariates. Covariates are selected a priori based on directed acyclic graphs (DAG) (Figure 4). Baseline covariates will be obtained from the CCHS questionnaire and include age (continuous), sex (binary categorical), smoking status (binary categorical), physical activity (hours/week, categorical), alcohol intake (number of standard drinks of beer, wine, spirits; continuous), and family history of cardiovascular disease, diabetes, hypertension, and hypercholesterolemia (binary precision variable). From the baseline clinical examination, we will obtain continuous measures of waist–hip ratio and serum lipid levels (precision variable). Register-based time-varying covariates for highest attained education (categorical) and income (continuous) will be obtained from Statistics Denmark, using data updated annually in the registers for the period between each participant’s baseline and follow-up visits. We will also adjust for baseline PFAS (continuous) if the correlation between baseline PFAS and the change is moderate (<0.8). All continuous covariates will be modeled using restricted cubic splines with 3 knots at the 10th, 50th, and 90th percentiles. We will assume temporality, with PFAS reduction occurring prior to serum lipids assessment and no reverse causation. We will assume consistency; that is, if two individuals exhibit the same measured reduction in PFAS, whether this results from increased excretion or from lower PFAS influx combined with natural excretion, they are considered to have experienced the same exposure for the purpose of the emulation. We will assume positivity, such that within strata defined by measured covariates, there is at least one participant in each PFAS-reduction group, allowing meaningful comparisons across exposure groups. As PFAS will be measured by the same accredited lab in one batch, we will assume that PFAS concentrations are measured accurately and comparably across visits. Because inclusion requires survival and participation in three visits over a 20-year period, a necessary assumption will be that, conditional on the above covariates, loss to follow-up is independent of potential serum lipid outcomes. This assumption is addressed in the methodological considerations section.

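### The reason given for not adjusting for dietary change is wrong for the effect of PFAS itself; it fits only a counseling effect, and the protocol mixes the two

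*Protocol article*

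**What the plan says.** The Introduction states the aim: "we aim to assess whether there is a causal relationship between PFAS and serum lipid levels by emulating a target trial". Section 2.2.3 defines the exposure: "intervention assignment will be inferred from the observed change in serum PFAS concentrations between the baseline and follow-up visit".

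Section 4 (Methodological Considerations) then makes these statements about diet:

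- Dietary change is a source of the exposure: "Behavioral dietary change (e.g., reduced consumption of animal-based foods) is part of the causal pathway through which PFAS exposure changes".
- Adjusting for it is rejected as "conditioning on a variable that created the PFAS change itself and would therefore result in removing part of the true causal effect" of reduced PFAS exposure.
- Reductions that come from dietary change "could influence serum lipids through nutritional pathways independent of PFAS".
- As a result, "any observed association between PFAS reduction and serum lipids may partly reflect concurrent lifestyle changes, potentially leading to an overestimation" of the true effect.
- The matter is treated as a threat to consistency. It is set aside because regulation is thought the likeliest driver and is said to act on everyone alike.

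Section 2.2.6 takes smoking, physical activity, alcohol and waist–hip ratio at baseline only. The time-varying covariates are education and income. Section 4 nevertheless describes rich longitudinal covariate data, "which will support the exchangeability assumption through adjustment for all identified confounders".

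**The concern.** A variable that produces the exposure lies upstream of it. Conditioning on such a variable cannot block the path from the exposure to the outcome. If the variable also affects the outcome by another route, leaving it out biases the estimate.

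The primary contrast is meant to answer whether PFAS causes higher lipids. If people whose PFAS fell also tended to improve their diet, lower lipids in the reduction group could come wholly or partly from diet. The protocol gives a reason not to look for this, and the reason does not apply to the effect it says it wants. Baseline covariates, including those offered as proxies for baseline diet, do not measure what changed over the following ten years.

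**Working it through.** The protocol gives no figure on this point, so there is none to reproduce. The check is one of causal structure, followed by an illustration.

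**1. Arrows taken from the protocol**

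| Arrow | Source |
|---|---|
| Diet change → PFAS change | Section 4: "Behavioral dietary change (e.g., reduced consumption of animal-based foods) is part of the causal pathway through which PFAS exposure changes" |
| Diet change → lipids, not through PFAS | Section 4: "could influence serum lipids through nutritional pathways independent of PFAS" |
| PFAS change → lipids | The effect under study (Introduction) |

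The open non-causal path is PFAS change ← diet change → lipids. Adjusting for diet change closes that path and leaves PFAS change → lipids intact. Section 4 treats baseline diet as a potential confounder because it affects both PFAS and lipids. Diet change meets the same criterion within the exposure window.

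**2. The uniformity argument**

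Write a person's PFAS change as a shared regulatory component plus an individual component. The shared component is the same for reducers and non-reducers, so it contributes nothing to the contrast. What separates the groups must be individual: diet and lifestyle, elimination, baseline level or measurement error. Uniform regulation therefore does not show that diet plays no part. Table 1 in fact reads the PFAS change as a marker of PFAS-related lifestyle change.

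**3. Which effect the argument would fit**

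The counseling trial in sections 2 and 2.1.2 and in Table 1 works through diet and lifestyle. For the effect of counseling, diet change belongs to the intervention and should not be adjusted away. The Introduction, and the sentence in section 4 on the effect of reducing PFAS exposure, concern PFAS itself. Both effects are in play and the protocol does not choose between them.

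**4. Illustration (all inputs assumed, none from the documents)**

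Let D be diet change and X a latent PFAS reduction, both standard normal with correlation ρ. A person is a reducer (A = 1) if X is in the top share p. Lipids are Y = βA − cD + noise, with β the true PFAS effect in SD units. The unadjusted difference between groups is

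β − cρ·φ(z)/[p(1 − p)],

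where z is the standard normal cut-off for share p and φ is the normal density.

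With ρ = 0.3, c = 0.3 and β = 0:

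- p = 0.5: 0.3 × 0.3 × 0.399/0.25 = 0.144, so −0.14 SD.
- p = 0.8: 0.3 × 0.3 × 0.280/0.16 = 0.158, so −0.16 SD.

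A simulation of 1,000,000 per scenario agrees:

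| True effect | p | Unadjusted | Adjusted for D |
|---|---|---|---|
| 0 | 0.5 | −0.141 | 0.002 |
| 0 | 0.8 | −0.160 | −0.002 |
| −0.20 | 0.5 | −0.344 | −0.201 |
| −0.20 | 0.8 | −0.361 | −0.202 |

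Over ρ from 0.1 to 0.5 and c from 0.1 to 0.3, the spurious difference with no PFAS effect runs from about −0.02 to −0.26 SD. At ρ = 0 it is zero. In every scenario adjustment returned the true effect and removed none of it.

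**5. Adjustment set against claim**

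Section 2.2.6 contains no measure of diet or lifestyle change. Section 4 identifies diet change as acting on both exposure and outcome. The statement that all identified confounders are adjusted for therefore does not hold for diet change.

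**The case against.** The strongest reply is that the target trial tests counseling, which works by changing diet and lifestyle; adjusting for those changes would move the emulation away from its own trial. This stands for a counseling effect. It does not rescue the sentence in section 4, which speaks of the effect of reducing PFAS exposure, or the aim in the Introduction.

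Second, the problem is disclosed with its direction. That also stands: the protocol is not silent. The disclosure is then neutralised by the uniformity argument, and neither sensitivity analysis in section 2.2.8 addresses it.

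Third, the illustration uses assumed inputs and a perfectly measured confounder, and it omits the planned baseline adjustments. This stands in full. It shows the direction and mechanism, not the size of bias in this cohort.

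Fourth, the remedy has limits. Baseline diet was not measured, so diet change cannot be computed. Section 2.2.1 says that each cycle had questionnaires and examinations but does not list the follow-up items. Waist–hip ratio, disease and medication at follow-up may be consequences of PFAS.

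A reader might go further and infer that exchangeability fails by the protocol's own account, or that a non-zero estimate must be expected even without a PFAS effect. The documents do not support this. Section 4 says only that the association may partly reflect lifestyle change, and the bias is zero if such change is unrelated to PFAS change. Nor does the protocol say that changes in smoking, alcohol or weight drive PFAS; its one example is diet. The covariate DAG (Figure 4) is not visible, so the claim about identified confounders may refer to that diagram.

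**Conclusion.** The point holds in a limited form. For the effect of PFAS itself, the stated reason for not adjusting for dietary change is wrong: on the protocol's own statements, diet change is a time-varying confounder and not a mediator. The uniformity argument does not remove the problem. The reasoning would be sound for PFAS reduction together with accompanying lifestyle change, but that is a different effect from the one in the Introduction.

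The size of the bias cannot be derived from the documents. The figure of about −0.15 SD is an illustration under an assumed correlation of 0.3, an assumed effect of 0.3 SD per SD and no PFAS effect. Under the document's arrows the bias is towards overstating the benefit of reduction if the dietary changes that lower PFAS also lower lipids, which is the direction section 4 itself concedes. The planned baseline covariates may remove part of it.

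**What to change.** 1. State whether the estimand is the effect of PFAS itself or of PFAS reduction together with accompanying lifestyle change.
2. If it is PFAS itself, withdraw the over-adjustment and uniformity arguments. Name diet and lifestyle change as time-varying confounding that is partly unmeasured, and correct the claim in section 4 that all identified confounders are adjusted for.
3. Pre-specify a sensitivity g-computation model that adds follow-up-visit smoking, alcohol and physical activity, and any diet item, where these were collected. Report it beside the primary result. Do not call the two results bounds: diet change may stay unmeasured in both, so the truth may lie outside the pair. Show follow-up waist–hip ratio only in a separate model labelled as possibly over-adjusted, and leave incident disease and medication out.
4. Because diet change stays unmeasured, either add a quantitative bias analysis over a stated range of correlations (including zero) and effects, or limit the conclusion to PFAS reduction plus accompanying lifestyle change.

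The cost is revised text, one or two further models, and some additional complete-case loss from the expected 655 participants. No further PFAS assays are needed.
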